#### Generalized linear regression sample code:

```
PROC GENMOD DATA=adeff DESCENDING;
```

|                                                                                                                                                                                                                                                                                                                                                   |
|---------------------------------------------------------------------------------------------------------------------------------------------------------------------------------------------------------------------------------------------------------------------------------------------------------------------------------------------------|
| CLASS TRTPN AVAL;
MODEL AVAL = TRTPN / DIST=BIN LINK=LOG;
where paramcd='DCA';
ESTIMATE 'Risk Ratio for TRTPN' TRTPN 1 -1 / EXP;
ODS OUTPUT Estimates=RRCL;
RUN;                                                                                                                         |
| Results Presentation                                                                                                                                                                                                                                                                                                                       |
| 
 
• Rate estimate and 95% CI can be retained from BinomialCL.
 
• Rate difference and 95% CI can be retained from diff.
 
• P value of non-inferiority test can be retained from noninf.
 
• Risk Ratio between TRA and TFA groups and its 95% CI can be retained from RRCL.
 
 |

#### 8.1.2.3.2. Model Specifications of Sensitivity Analysis

Same as primary analysis.

## 8.2. Secondary Efficacy Endpoints Analyses

### 8.2.1. Overview of Planned Secondary Efficacy Endpoints Analyses

The secondary endpoints analyses for efficacy will be based on the [FAS](#) population, unless otherwise specified.

Table 5 provides an overview of the planned secondary endpoints analyses for efficacy.

**Table 5 Overview of Planned Secondary Endpoints Analyses for Efficacy**

|                                              | Data Displays Generated |        |         |
|----------------------------------------------|-------------------------|--------|---------|
|                                              | Table                   | Figure | Listing |
| Rate of Successful Accurate Diagnosis |                         |        |         |
| Descriptive statistics:                      | Y                       |        | Y       |

|                                                                                                                                                                               | Data Displays Generated |        |         |
|-------------------------------------------------------------------------------------------------------------------------------------------------------------------------------|-------------------------|--------|---------|
|                                                                                                                                                                               | Table                   | Figure | Listing |
| 

– Number of subjects with successful accurate diagnosis

– Success rate of accurate diagnosis with 95% CI

              |                         |        |         |
| Difference in rates of successful diagnosis between TRA and TFA groups and its 95% CI                                                                                         |                         |        |         |
| Risk Ratio (RR) between TRA and TFA groups and its 95% CI                                                                                                                     |                         |        |         |
| Duration of Angiography (min)                                                                                                                                                 |                         |        |         |
| Descriptive statistics: 

– Number of non-missing subjects (n)

– Mean (SD)

– Median (Q1, Q3)

– Min, Max

 | Y                       |        | Y       |
| Difference in duration of angiography between TRA and TFA groups and its 95% CI                                                                                               |                         |        |         |
| Duration of Fluoroscopy (min)                                                                                                                                                 |                         |        |         |
| Descriptive statistics: 

– Number of non-missing subjects (n)

– Mean (SD)

– Median (Q1, Q3)

– Min, Max

 | Y                       |        | Y       |
| Difference in duration of fluoroscopy between TRA and TFA groups and its 95% CI                                                                                               |                         |        |         |
| Flat Time (Hours)                                                                                                                                                             |                         |        |         |
| Descriptive statistics: 

– Number of non-missing subjects (n)

– Mean (SD)

– Median (Q1, Q3)

– Min, Max

 | Y                       |        | Y       |
| Difference in flat time between TRA and TFA groups and its 95% CI                                                                                                             |                         |        |         |

|                                                                                                                                   | Data Displays Generated |        |         |
|-----------------------------------------------------------------------------------------------------------------------------------|-------------------------|--------|---------|
|                                                                                                                                   | Table                   | Figure | Listing |
| Visual Analogue Scale (VAS) Score (within 24h)                                                                             |                         |        |         |
| Descriptive statistics:
– Number of non-missing subjects (n)
– Mean (standard deviation)
– Median (Q1, Q3)
– Min, Max | Y                       |        | Y       |
| Difference in VAS score between TRA and TFA groups and its 95% CI                                                                 |                         |        |         |

## 8.2.2. Specifications of Secondary Efficacy Endpoints Analyses

### 8.2.2.1. Definitions and Derivations

- Success rate of accurate diagnosis: successful accurate diagnosis is defined as the aortic arch vessel is successfully superselected without changing the puncture site, with angiography results meeting the diagnostic requirements.
- Duration of angiography (min): Time from puncture to the end of the angiography.
- Duration of fluoroscopy (min): data from the machine will be used.
- Flat time: Time (hours) from the end of the procedure to ambulation. If the minute of the flat time is unknown, it will be imputed as 30 minutes. If both hour and minute are unknown, it will be treated as missing data.
- Visual Analogue Scale (VAS) score: The VAS will be completed within 24 hours after the end of the angiography.

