**Success rate of diagnostic cerebral angiography**

Successful diagnostic angiography: the aortic arch vessel is successfully selected without changing the puncture site, with angiography results meeting the diagnostic requirements.

For intraoperative management, please refers to *Chinese Expert Consensus on Good Practice for Cerebral Angiography (2018)*.

In case of angiography failure, record in which of the following stages it occurs and why it occurs:

Stage 1: Unable to insert the arterial sheath (small artery diameter, no blood return after arterial puncture, unable to advance the guidewire due to vasospasm, and atherosclerotic plaque, etc.);

Stage 2: Puncture and sheath placement is successful, but the catheter or guidewire cannot be advanced (arterial tortuosity, vasospasm, and loop, etc.);

Stage 3: The guidewire and catheter has reached the aortic arch, but the primary branch of the aortic arch cannot be selected;

Stage 4: The guidewire and catheter has reached the primary branch of the aortic arch, but the procedure still cannot be completed successfully;

➤ **Secondary Effectiveness Endpoints:**

- Success rate of accurate diagnosis: successful accurate diagnosis is defined as the responsible vessel for the disease is successfully superselected without changing the puncture site, with angiography results meeting the diagnostic requirements.
- Duration of angiography: Time from puncture to the end of the angiography.
- Duration of fluoroscopy: Data from the machine will be used.
- Bedridden time: Time (hours) from the end of the procedure to ambulation.
- Visual Analogue Scale (VAS) score: The VAS will be completed within 24 hours after the end of the angiography. The VAS is provided in Appendix 3.

(2) Safety Endpoints:

- Incidences of angiographic complications during and within 24 hours after the procedure
- Incidences of major angiographic complications during and within 24 hours after the procedure

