## 5. Study Interventions

### 5.1 Standard Operating Procedures for TRA and TRF Cerebral Angiography

#### Transfemoral cerebral angiography:

**Aortic arch angiography:** With the progress of angiography technique and the need of higher safety, it is currently believed that aortic arch angiography can help to preliminarily evaluate the overall intracranial and external vascular conditions, so as to find vascular orifices above the arch and select appropriate catheters, facilitating the operating for digital subtraction angiography (DSA). Aortic arch angiography is usually performed using a hydrophilic guidewire with a diameter of 0.035 inch (1 inch = 2.54 cm) and a pigtail catheter with side holes. The end of the catheter will be directly connected to the pressure extension tube of the DSA high pressure syringe by automatic injection.

**Selective angiography:** Standard cerebrovascular angiography is a quadruple angiography including bilateral internal carotid/common carotid artery + bilateral vertebral artery angiography. Sometimes, a bilateral external carotid artery angiography is also needed to confirm compensation of external cranial artery or to exclude dural arteriovenous fistula. However, in order to reduce the risk of plaque detachment caused by guidewire contact with the arterial plaque, in most cases, quadruple angiography (i.e. bilateral common carotid artery + bilateral subclavian artery angiography) is considered

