to be sufficient to clearly observe the intracranial and extracranial vessels. Quadruple angiography is usually completed by using a hydrophilic guidewire of 0.035 inch and a single curved angiographic catheter (such as a Vertebral catheter). Manipulation steps: (1) Connection: Connect the end of the single curve catheter in conjunction with a guidewire to a Y shaped valve, and then connect it to pressure drip and high-pressure syringe via a three-way pipe to drain the air in the pipeline. (2) Catheterization: Advance the catheter to the ascending aorta through the aortic arch under the guidance of an angiographic guidewire, and withdraw the guidewire. Slowly withdraw the catheter while rotating at the same time until the tip of the catheter is catapulted into the orifice of the primary vessel of the arch. At this time, advance the guidewire to ensure the supporting force of the guidewire is sufficient to support the catheter and keep the tip of the guidewire within the safe area. Fix the guidewire and advance the catheter slowly along the guidewire. During carotid angiography, the catheter tip should be placed at 2 to 3 cm below the carotid bifurcation. During subclavian artery and vertebral artery angiography, the catheter tip should be placed in the subclavian artery at 1 to 2 cm from the orifice of the vertebral artery. (3) Angiography. Angiography with the catheter tip located in the primary branch of the aortic arch is usually called selective angiography. Angiography with the catheter tip located in any secondary or even tertiary branch, such as the internal carotid and vertebral arteries, is called super-selective angiography. The diameters of these branches are small, so it is recommended to accurately deliver the guidewire into the target blood vessel under the guidance of the road map of selective angiography, and then keep the angiography catheter coaxial with the target blood vessel and advance it to a proper position suitable for angiography. Precautions during the procedure: (1) Before super-selective angiography, the diameter and tortuosity of the target vessel should be carefully evaluated, and make judgement by considering the necessity of super-selective angiography comprehensively. Super-selective angiography should be performed with caution if there is plaque or stenosis in the vessel orifice. (2) The target vessels of super-selective angiography are more likely to be injured, and the guidewire should be pushed gently with appropriate rotation, to avoid vascular dissection. (3) If there is severe stenosis or aneurysm in the target

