### **7.7.1 Primary Effectiveness Analysis**

The primary effectiveness endpoint of this study is the success rate of diagnostic cerebral angiography, which is defined as the aortic arch vessel is successfully selected without changing the puncture site, with angiography results meeting the diagnostic requirements. Any change of puncture site before or during the procedure after a subject has been randomized would be treated as a diagnosis failure.

The success rate and failure rate of diagnosis will be described, and the causes of failure will be summarized (see Section 2.2 Study Endpoints for details). The Clopper-Pearson method will be used to calculate the 95% confidence intervals (CI) for rate of successful diagnosis in both groups, as well as the difference in rates between the two groups and its 95% CI (Miettinen-Nurminen method). Chi-square tests will be used for non-inferiority tests for rates of successful diagnosis in both groups, and Logistic regression will be used to calculate odds ratio (OR) between the two groups and its 95% CI.

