## 8.1.2. Specifications of Primary Efficacy Endpoint(s) Analyses

### 8.1.2.1. Definitions and Derivations

The primary effectiveness endpoint of this study is the rate of successful diagnostic cerebral angiography, which is defined as the aortic arch vessel is successfully superselected without changing the puncture site, with angiography results meeting the diagnostic requirements. Any change of puncture site before or during the procedure after a subject has been randomized would be treated as a diagnosis failure.

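### SAP 8.2.2.1 gives the secondary endpoint of accurate diagnosis the primary endpoint's definition, and the SAP also changes the primary's verb; Table 1 declares neither

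*Combined protocol and SAP*

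**What the plan says.** **Protocol.** Section 2.2 defines primary success as "the aortic arch vessel is successfully selected without changing the puncture site, with angiography results meeting the diagnostic requirements". The synopsis and Section 7.7.1 say the same (7.7.1: "which is defined as the aortic arch vessel is successfully selected without changing the puncture site"). For the secondary endpoint, Section 2.2 says "successful accurate diagnosis is defined as the responsible vessel for the disease is successfully superselected without changing the puncture site", again with results that meet the diagnostic requirements.

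Section 5.1 gives the two verbs different meanings: "Angiography with the catheter tip located in the primary branch of the aortic arch is usually called selective angiography", whereas a tip in a secondary or tertiary branch, such as the internal carotid or vertebral artery, makes it super-selective. Under its transfemoral heading it adds that "in most cases, quadruple angiography (i.e. bilateral common carotid artery + bilateral subclavian artery angiography) is considered" enough to show the intracranial and extracranial vessels.

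**SAP.** Section 8.1.2.1 has the primary "defined as the aortic arch vessel is successfully superselected without changing the puncture site, with angiography results meeting the diagnostic requirements", and the objectives table in Section 1.2 uses the same verb. Section 8.2.2.1 then states for the secondary that "successful accurate diagnosis is defined as the aortic arch vessel is successfully superselected without changing the puncture site", with the same condition on the results. Section 8.2.2.2 analyses accurate diagnosis in a similar way to the primary, and Tables 4 and 5 plan separate displays for the two.

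Section 1.1 says that Table 1 sets out any changes from the protocol's planned analysis. Table 1 covers the confidence interval method, the test, and the risk ratio in place of the odds ratio. It mentions no endpoint definition.

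**The concern.** Taken at its word, the SAP has one binary efficacy outcome under two names, and Table 5 would repeat the result in Table 4. The outcome that disappears is an informative one: Protocol 3.2 says that superselecting vessels is harder by the radial route, and the responsible-vessel endpoint is the planned look at that.

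The change of verb touches the primary itself. If the terms in Protocol 5.1 govern, a complete, diagnostic study done by selective angiography alone meets the protocol's primary definition but might not meet the SAP's. The 97% and 98% assumptions and the -5% margin were set for the protocol's endpoint.

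**Working it through.** **1. The four definitions side by side.**

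| Endpoint | Vessel | Act | Puncture site | Images |
|---|---|---|---|---|
| Primary, Protocol 2.2 and 7.7.1 | aortic arch vessel | selected | unchanged | diagnostic |
| Primary, SAP 1.2 and 8.1.2.1 | aortic arch vessel | superselected | unchanged | diagnostic |
| Accurate diagnosis, Protocol 2.2 | responsible vessel | superselected | unchanged | diagnostic |
| Accurate diagnosis, SAP 8.2.2.1 | aortic arch vessel | superselected | unchanged | diagnostic |

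The two protocol rows differ in vessel and act. The two SAP rows differ in nothing. The primary changed its verb, the secondary changed its vessel, and Table 1 declares 0 of these 2 changes.

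**2. Consequence for the secondary.** Under the protocol a patient can succeed on the primary and fail accurate diagnosis: the arch vessel is selected but the responsible vessel is not superselected. Under the SAP text that cell of the cross-table is empty by definition. SAP 8.1.2.1 also counts any change of puncture site after randomization as a failure. This restores no difference, because both definitions already require an unchanged site.

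**3. Consequence for the primary.** The list of failure stages in Protocol 2.2 fits *selected*: Stage 3 is failure to select a primary branch of the arch. Under the Protocol 5.1 terms, *superselected* asks for more. The documents do not give the share of studies completed by selective angiography only, so no reclassification count can be derived.

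**4. The plan's sample size.** Inputs from Protocol 7.3: 97% for TRA, 98% for TFA, margin 5 points, power 90%, one-sided 0.025, drop-out 10%, 429 per group.
- Evaluable per group: 429 × 0.9 = 386.1, so 386. Check: 386 / 0.9 = 428.9, rounded up to 429.
- Score test with binomial enumeration at 386 per group: power 89.2%. Power first passes 90% at 394, and 394 / 0.9 gives 438, within 3% of 429.
- The simple unpooled normal formula gives 320, or 356 after drop-out.

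The documents do not name the PASS procedure. The figure reproduces with a score test, and restoring the protocol wording alters none of its inputs.

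**5. How reclassification would act (illustration on assumed rates that the documents do not give).** With p_T for TRA and p_F for TFA:

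power ≈ Φ( [0.05 − (p_F − p_T)] / se − 1.96 ), se = √{ [p_T(1 − p_T) + p_F(1 − p_F)] / 386 }

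At 98/97 (TFA/TRA): se = √(0.0487/386) = 0.01123, and Φ(0.04/0.01123 − 1.96) = Φ(1.60) = 95%. Enumerating the SAP's Wald test gives 93%.

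*Both arms fall, with the 1-point difference held:*

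| TFA/TRA, % | Formula | Enumerated |
|---|---|---|
| 98/97 | 95% | 93% |
| 96/95 | 76% | 76% |
| 95/94 | 68% | 69% |
| 93/92 | 56% | 56% |
| 90/89 | 44% | 44% |

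*Only TRA falls (formula):* 98/96 gives 69% and 98/95 gives 33%.

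In the first case the true difference stays at -1 point and the loss is one of precision. In the second it moves to -2 or -3 points, towards the margin.

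**The case against.** **Loose usage.** A reader might infer that the SAP has redefined the primary, so that every selective-only study becomes a failure. The documents do not establish that. Protocol 5.1 separates the two terms, but only as what they are usually called. Section 10.3 applies superselective angiography to the great vessels of the arch as well as their branches. Section 3.2 illustrates superselection with success rates that start at the right subclavian artery, which Section 5.1 counts among the great vessels. The introduction has the catheter loop superselecting the target vessel from the arch. The SAP's object is still the aortic arch vessel, so a translation or copying slip is a natural reading. This stands: the stricter primary is one literal reading.

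**Outcomes may not be derived from the SAP sentence.** Protocol 11.7 sends both endpoints to independent third-party imaging assessment. The SAP (dated January 2025) cites an eCRF of April 2024, and its risk-ratio code picks the primary by a parameter code. The data may already follow the protocol's wording. This stands too, but the documents shown do not say so, and it does not correct the SAP text.

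**The margin.** A reader might also infer that a selective-only share above a few percent would by itself exceed the 5-point margin. It would not. That share applies within arms, whereas the margin applies to the difference between arms. Step 5 shows the distinction.

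**Selective angiography as the norm.** The sentence calling four-vessel selective study sufficient in most cases stands under the transfemoral heading. The radial text asks for superselection where there is an intracranial lesion or a cervical vessel needs separate evaluation. The sentence should not be extended to the whole trial, although the radial text also lets angiography be completed from the great vessels.

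**Conclusion.** The secondary-endpoint part holds in full on the text. SAP 8.2.2.1 repeats the primary's defining clause and drops the responsible vessel, and an analysis that follows it as written would report the primary twice.

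The primary-endpoint part holds as an undeclared change of verb that leaves the definition open to a stricter reading. It is not an established redefinition, and its effect cannot be sized: the documents give neither a selective-only count by arm nor the definition that the eCRF or the committee used. The power figures above rest on assumed rates and show only the mechanism. The loss of the secondary endpoint in the results likewise assumes that it is derived from the SAP sentence. The sample size of 429 per group, 858 in total, is unaffected.

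**What to change.** 1. In SAP 8.2.2.1 restore the protocol's definition: "successful accurate diagnosis is defined as the responsible vessel for the disease is successfully superselected without changing the puncture site", with results that meet the diagnostic requirements.
2. In SAP 1.2 and 8.1.2.1 restore "the aortic arch vessel is successfully selected without changing the puncture site, with angiography results meeting the diagnostic requirements".
3. Before database release, confirm from the eCRF and the imaging committee's instructions that the two endpoints come from distinct assessments made under the protocol definitions, and record the answer in the SAP.
4. If either change was intended, declare it in Table 1 with a reason. For the primary, also say whether the assumed rates and the margin still apply.

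The cost is three wording corrections and a check of two derivations. No sample-size figure and no analysis method changes.
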